## Abstract

**Background:**

Adolescents who use alcohol and other drugs on school campuses are at heightened risk for adverse consequences to their health and wellbeing. Schools have historically turned to punitive approaches as a first-line response to substance use. However, punishment is an ineffective deterrent for substance use and may cause harm and increase inequities. iDECIDE (Drug Education Curriculum: Intervention, Diversion, and Empowerment) was developed as a scalable and youth-centered drug education and diversion program that can be used as a skills-based alternative to punishment. We aim to evaluate the effectiveness of the iDECIDE curriculum as an alternative to punishment (ATP) for school-based substance use infractions in the context of a large pragmatic clinical effectiveness study.

**Methods:**

We will conduct a Type 1, hybrid effectiveness-implementation trial. Using a stepped wedge design with approximately 90 middle and high schools in Massachusetts, we will randomly allocate the timing of implementation of the iDECIDE curriculum compared to standard disciplinary response over approximately 36 months. We will test the overarching hypothesis that student-level outcomes (knowledge of drug effects and attitudes about substance use; frequency of substance use; school connectedness) improve over time as schools transition from a standard disciplinary response to having access to iDECIDE. The secondary aims of this trial are to (1) explore whether change in student-level outcomes vary according to baseline substance use, number of peers who use alcohol or other drugs, age, gender, and school urbanicity, and (2) determine the acceptability and feasibility of the iDECIDE curriculum through qualitative stakeholder interviews.

**Discussion:**

Substance use continues to be a major and rapidly evolving problem in schools. The importance of moving away from punishment to more restorative approaches is widely accepted; however, scalable alternatives have not yet been identified. This will be the first study to our knowledge to systematically evaluate an ATP for students who violate the school substance use policy and is well poised to have important implications for policy making.

## 1. Introduction

In 2022 ~7%, 13%, and 22% of 8th, 10th, and 12th-grade students, respectively, in the U.S. reported using any illicit substance in the past 30 days (1). Middle and high school campuses have become a common point of access for alcohol and other drugs. According to the Massachusetts Department of Elementary and Secondary Education (DESE), rates of chemical health violations increased 27% in the 2 years leading up to COVID-19 quarantine (2). This rise in at-school substance use is in part due to the advent of electronic cigarettes and other vaping devices that have become increasingly popular, inconspicuous, and concealable from peers and school personnel (3). Compared with out-of-school use, in-school substance use is associated with increased odds of intoxicated driving, fighting, weapon-carrying at school, risky sexual behavior, sexual assault, intimate partner violence, depression, suicidal ideation, and attempted suicide (4). It is thus a priority for schools to define effective responses to this emerging problem to mitigate risk for adverse consequences to health and wellbeing.

Schools have historically relied on exclusionary, punitive responses (e.g., detention, suspension, expulsion) to address violations to school substance use policy. However, punitive approaches are not only ineffective deterrents for substance use (5–7), but may also increase risk for substance use escalation (8, 9), academic difficulties (9–11), disengagement from school (10), and delinquency (12, 13). Moreover, being suspended only once in 9th grade increases risk of drop-out by three-fold (14–16). There are several pathways by which punishment can catalyze negative outcomes, including increased unsupervised time, alienation from peers, reactivity, and disconnection from school supports, resources, and services (17, 18). Punitive responses may also stigmatize and label students, with possible effects including deteriation of trust and breakdown of student-school relationships (19). Supportive, alternative to punishment (ATP) responses to youth substance use infractions provide greater opportunities for students to build positive relationships with a trusting, caring adult at school, improving school connectedness and possibly reducing future infraction rates (20). Finally, punitive responses are a missed opportunity for early intervention as they fail to address the multitude of factors that may lead an adolescent to initiate or escalate substance use (e.g., attempt to fit in with peers, manage internalizing symptoms, avoid environmental stressors) (3). Supportive ATP, like diversion programs, can uncover underlying motivations for substance use and align goals with core values, increasing the likelihood of lasting behavior change.

To determine the need for ATPs in middle and high schools across Massachusetts, this study team conducted a statewide survey in May-June 2020 of school stakeholders, including district administrators, principals and vice principals, school resource officers, guidance counselors, and nurses (21). The survey asked about beliefs, attitudes, and actions that schools take regarding school-based substance use infractions as well as perceived barriers to implementing diversion programs. Most stakeholders reported that while the most common response to substance use in their school/district included some sort of punishment (85.3%), ATPs including diversion programs were perceived to be more effective than punishment. Multiple barriers to implementation of ATPs were identified including lack of availability of curriculum that address substances beyond nicotine. These preliminary data highlight widespread interest in but limited access to evidence-based ATPs.

Availability of scalable, sustainable, and evidence-based ATPs may also be an important step in bridging racial disparities, as Black, Indigenous, and other Youth of Color (BIYOC) and those in resource-limited settings are disproportionately impacted by punitive approaches for school-based substance use infractions (11, 13). According to the 2017–2018 data from the U.S. Department of Education's Office of Civil Rights, Black students were suspended almost three times as often as white students and were referred to law enforcement more than two times as often for infractions that took place on school campuses (22). Meaningful steps are urgently needed to limit the inequitable use of punishment for substance use at school to improve individual- and community-level outcomes, interrupt the school-to-prison pipeline, and begin to dismantle sources of structural racism.

The primary aim of this study is to evaluate the effectiveness of iDECIDE (Drug Education Curriculum: Intervention, Diversion, and Empowerment), a novel, free, state-funded (Massachusetts Department of Public Health, MA DPH) substance use diversion program in the context of a large pragmatic clinical effectiveness study. We will test the overarching hypothesis that student-level outcomes (i.e., knowledge of drug effects, attitudes about substance use, frequency of substance use, and school connectedness) improve over time as schools transition from standard disciplinary responses to having access to iDECIDE, an educational and therapeutic ATP. Secondary aims of this trial are to (1) explore whether change in student-level outcomes varies according to baseline substance use, number of peers who use alcohol or other drugs, age, sex, gender, and school urbanicity, and (2) determine the acceptability and feasibility of the iDECIDE curriculum as an ATP for school-based substance use infractions.

## 2. Materials and methods

### 2.1. Design

We will conduct a Type 1, hybrid effectiveness-implementation trial (23) guided by Proctor's implementation model (24). Using a stepped wedge design with approximately 90 schools, we will randomly allocate the timing of implementation of the iDECIDE curriculum compared to standard disciplinary response, over approximately 36 months. Timing of curriculum implementation will be staggered over seven clusters, with each cluster composed of ~7–15 schools (size of clusters accounting for districts randomized together). One cluster of schools will cross from control (unexposed phase) to intervention (exposed phase) approximately every two to three school months until all schools are exposed to iDECIDE. This design will allow transition periods for training of school-based facilitators, during which clusters will not be considered as either in the control (unexposed) or intervention (exposed) phase of the study. See Figure 1 for the approximate stepped wedge schema.

**Figure 1 F1:**
[figure not shown]
Stepped wedge schema.

Data collection will occur during both unexposed and exposed study phases. School staff will refer students with school-based substance use infractions to the study team as close to the time of infraction as possible through an online, secure referral system. Referrals will be submitted while schools are in both unexposed and exposed study phases. Once referred to the study team, students will be given the opportunity to enroll in a three visit study. Baseline visits will occur as close as possible to the receipt of school referrals to establish information most representative of thoughts, feelings, and behaviors at the time of the initial infraction. Follow-up visits will occur ~45 and 90 days after the baseline visit to ascertain thoughts, feelings, and behaviors occurring after the time of the school response to the substance use infraction, which may or may not involve iDECIDE depending on whether the school is in the unexposed or exposed phase of the study. Study procedures will take place remotely, at the student's school, in a private space at a local public library, or at the Massachusetts General Hospital (MGH) lab based on the preferences of the school, student, and/or parent/guardian.

This trial has been approved by the Mass General Brigham (MGB) Institutional Review Board (IRB). The trial will be conducted in accordance with the Consolidated Standards for Reporting Trials (CONSORT) statement (25–28) and will be reported here in accordance with the Standard Protocol Items: Recommendations for Intervention Trials (SPIRIT) statement (29, 30).

### 2.2. Partnering schools

Middle and high schools across all 351 municipalities in Massachusetts were given the opportunity to participate in this trial. Proactive school recruitment occurred across a period of approximately 12 months. Schools had the opportunity to attend an informational session about iDECIDE and/or meet one-on-one with members of the evaluation team to discuss study involvement. Recruitment for schools occurred through state listservs, word of mouth, and facilitated introductions through DPH, local community coalitions, and other community agencies. Inclusion criteria for schools include (1) middle or high school, serving grades 6-12, (2) agreement to refer students with a school-based substance use infraction to the MGH evaluation team (unless opted out by the student's parent/legal guardian; see section on Consent or Assent below), and (3) a signed letter of commitment from the appropriate school/district representative.

The first school cohort was enrolled in January 2022 (Cohort 1; *n*_schools_ = 69 schools). Due to substantial unsolicited interest in the curriculum from schools following the return to in-person learning after the COVID-19 pandemic, one additional wave of schools was onboarded and separately randomized in September 2022 (Cohort 2; *n*_schools_ = 33 schools).

### 2.3. Participants and recruitment

Participants will be recruited by direct school referral only. Parents/guardians will have the opportunity to opt their students out of the referral process at the beginning of each school year. Upon receipt of a school referral, the MGH evaluation team will invite the student to participate in the trial. Students will be eligible to participate if they were not opted out by the parent/guardian, recently referred for a substance use-related infraction at school or at a school-sanctioned event, are able to read and write comfortably in English, Spanish, or Portuguese, and are able to safely participate in the protocol in the opinion of the investigator. Participants will be reimbursed $50 per visit plus bonuses for urine samples for toxicology testing ($10/per sample/per visit) and a saliva sample for genetic testing ($5), totaling up to $185. Payment will be distributed via check or gift card at the end of all three visits.

### 2.4. Consent or assent

Once a referral is received, the MGH evaluation team will contact the student and their parent/guardian to seek written informed consent/assent prior to initiating any further study procedures. Once parent/legal guardian consent is obtained, eligible participants will provide assent following verbal and written explanation of the study, potential risks and voluntary nature of participation, right to withdraw, and details of data protection and confidentiality. Parental permission will not be required for students ages 18 and older.

### 2.5. Randomization

We will randomly allocate the timing of implementation of the iDECIDE program (vs. standard disciplinary response). Schools will be randomly phased into iDECIDE over the course of the trial (exposed phase; see Figure 1). When a school is randomized to iDECIDE, school staff will be trained as facilitators in the curriculum but will retain discretion as to which students should be enrolled in the program. To avoid risk of contamination bias within a school or district, school districts will serve as the unit of randomization with all schools within the same district randomized together. Randomization will occur by district, and stratified by (a) whether a district has any middle schools (yes/no) and (b) the number of total students in a district (low/high, using a median-split applied separately to the groups defined in (a) to ensure sufficient districts to distribute across waves). This stratification approach should help address differences in infraction rates for middle schools vs. high schools, and how smaller schools will, by necessity, have fewer potential participants. Cohorts 1 and 2 were randomized separately.

### 2.6. Blinding

Outcome assessors will be blinded to the school randomization phase. To avoid detection bias toward adjustments that favor statistical significance, initial implementation of analyses will also be “analyst-blind” (31). Only once data exclusion criteria have been finalized, models have been properly specified, and any other unforeseen circumstances have been addressed, will the unshuffled data be provided to the analyst for the final analysis implementation.

### 2.7. Interventions

#### 2.7.1. Discipline as usual

Standard disciplinary responses given by each partnering school will be used as the control during the unexposed phase of this trial. Standard responses may include detention, Saturday school, in-school suspension, out-of-school suspension, expulsion, citation, or any other punitive or non-punitive response given by schools per their existing policy at the point of a violation of school substance use policy. Students will report on the school response to the infraction during the baseline assessment.

#### 2.7.2. iDECIDE curriculum

Schools will be randomly phased into iDECIDE over the course of the trial (exposed phase; see Figure 1 and Section 2.5.).^1^ When a school is randomized to iDECIDE, school staff will be trained as facilitators in the curriculum but will retain discretion as to which students should be enrolled in the program.

iDECIDE promotes education and empowerment, instead of punishment, as an equitable response to adolescent substance use (1). Providing youth with science-based information and critical skills, iDECIDE challenges youth to make decisions that align with their core values, future goals, and support of their own personal wellbeing. While iDECIDE was designed as an ATP, it can be used outside of an infraction context as a targeted prevention for adolescents who are experimenting or are at risk for experimenting with substances. iDECIDE is intended to be slotted within tier 2 supports, or early indicated intervention, of school-based multi-tiered systems of support (32)—it is not a replacement for tier 1 universal prevention programming, nor is meant to be used in lieu of treatment or more intensive services when clinically indicated.

Curriculum development was guided by ongoing feedback from students and key school and community stakeholders. The iDECIDE curriculum is administered by a trained adult facilitator (see 2.7.2.1 below) in either a 1:1 or group setting. The curriculum consists of four core modules, each ~60–75-min in length. Module content covers teen brain development, neurobiology and addiction, industry tactics, risk and protective factors, drug effects, motives and triggers for use, healthy alternatives, mindfulness and meditation, core values, and goal setting (Table 1). The curriculum content is delivered through different modalities including educational videos, worksheets, handouts, group discussions, and on-your-own assignments. iDECIDE is drug agnostic, covering psychoeducational material relevant to alcohol, cannabis, nicotine, and other drugs. All information is hosted through an online learning management system. The curriculum, including all the supportive materail, is ADA-accessible and is available in English, Spanish, and Portuguese.

**Table 1 T1:** Overview of the iDECIDE curriculum.

**Module**	**Name**	**Content**
1	Teen brain development, neurobiology and addiction, and industry tactics	Learn about neurobiology and addiction with a focus on teen brain development, industry tactics that target teens and other vulnerable populations, and their personal risk and protective factors for substance use and addiction.
2	Motives for use and specific drug effects	Learn about the neurobiology and effects of alcohol and other drugs on the brain and body. Assess substance use behavior and how it affects one's life.
3	Identifying triggers and healthy alternatives	Define and identify internal and external triggers to use alcohol and other drugs. Establish healthy alternatives to deal with urges to use substances by identifying realistic substance-free alternatives, developing effective communication strategies, and engage in mindfulness techniques.
4	Core values and setting goals	Identify core values, set short- and long-term goals that move toward overall wellness, and set actionable goal related to substance use that supports a healthier lifestyle and aligns with individual core values.

##### 2.7.2.1. Facilitator training

Individuals within each school will be identified to be trained as facilitators once a school has been randomized to transition from the unexposed to exposed phase of the study. Clinical training will not be required to serve as an iDECIDE facilitator. Facilitators will be required to attend a free, one-day, live training offered by MGH and MA DPH before gain access to any of the curriculum materials. During the training, facilitators will review the curriculum, gain access to the learning management system, and will cover other topics helpful in facilitating iDECIDE (e.g., motivational interviewing, managing unanticipated situations, and culturally responsive approaches). Facilitators will receive a copy of the facilitator manual and a participant workbook during their training. Each facilitator will be required to complete an annual fidelity check to maintain their certification as an iDECIDE facilitator. The fidelity check can be the option to re-attend a live training or have a designated iDECIDE team member observe and rate a live, recorded, or practice session of the curriculum.

### 2.8. Outcome measures

Assessments will occur at baseline (proximal to the point of the initial infraction), and ~45- and 90-days following baseline. Primary, secondary, and exploratory outcomes are described below. All measures, including descriptives and potential covariates, are listed in Table 2.

**Table 2 T2:** Time and events.

**Assessments**	**Baseline (V1)**	**45-day follow-up (V2)**	**90-day follow-up (V3)**
**Primary outcomes**			
Knowledge of drug effects	X	X	X
Timeline follow-back	X	X^*^	X^*^
Urinalysis	X	X	X
**Secondary/exploratory outcomes**			
School climate measure	X	X	X
Infraction information survey	X	X	X
**Descriptions, effect modifiers, covariates**			
Demographics	X	-	-
Concomitant medications	X	X	X
Adverse events	-	X	X
MINI	X	-	-
C-SSRS	X	-	-
Participant psychiatric history	X	-	-
Family psychiatric history	X	-	-
UPPS-SP	-	-	-
AUDIT	X	-	-
CUDIT	X	-	-
FTND	X	-	-
ECDI	X	-	-
ASRI	X	-	-
MCQ delay discounting	X	-	-
Substance use history	X	-	-
Peer/partner substance use and tolerance of substance use	X	X	X
House rules about substance use	X	-	-

* means: a modified TLFB will be administered at V2 and V3 to gather substance use between visits.

#### 2.8.1. Primary outcome: knowledge of drug effects

The knowledge of drug effects will be operationalized as number of items correct on a custom-designed survey examining a student's understanding of the impact of alcohol, cannabis, nicotine, and other drugs on the brain and body, assessed at all three time points.

#### 2.8.2. Primary outcome: frequency of substance use

Substance use behavior will be assessed by how many days of the past 14 days a student spent using their preferred substance. Self-reported substance use will be assessed at all visits using the Timeline Followback (33, 34). A 90-day recall period will be queried at enrollment, and a modified Timeline Followback will be administered at subsequent visits to ascertain substance use in the period between visits.

Urine samples will be collected at all three visits to biochemically verify self-reported use. A 10-panel qualitative rapid dip drug test (Medimpex United Inc.) will be performed, qualitatively assessing for amphetamines (limit of quantitation [LOQ] = 1,000 ng/mL), cocaine (LOQ = 300 ng/mL), barbiturates (LOQ = 300 ng/mL), methamphetamines (LOQ = 1,000 ng/mL), benzodiazepines (LOQ 300 ng/mL), opiates (LOQ = 2,000 ng/mL), cannabinoids (THC) (LOQ 50 ng/mL), phencyclidine (LOQ = 25 ng/mL), oxycodone (LOQ = 100 ng/mL), and methadone (LOQ = 300 ng/mL). Quantitative urinary assays will also be completed at all visits (Dominion Diagnostics, North Kingstown, Rhode Island, USA). The quantitative assay includes creatinine-normalized 11-nor-9-carboxy-THC levels (CN–THCCOOH; LOQ: 5 ng/mg; upper limit of linearity: 500 ng/mg) using liquid chromatography–tandem mass spectrometry, and cotinine via enzyme immunoassay (EIA; LOQ: 500 ng/mL; upper limit of linearity: 2,000 ng/mL). Study staff will mail collection kits in advance of virtual visits to participants, and participants will provide the sample during the videoconferencing session. Qualitative results will be shown to the assessor during the visit, and kits will be shipped overnight for quantitative assays.

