### 2.10. Data analysis

#### 2.10.1. Overarching statistical model

The two primary outcomes will be assessed at three time points: (1) immediately after a student is first caught for a substance use infraction (i.e., baseline, *time-of-infraction*); (2) 45 days after the date of the first infraction (i.e., *45 day-follow-up*); (3) 90 days after the date of the first infraction (i.e., *90 day-follow-up*). The proposed primary outcomes (items correct on a knowledge survey and number of days out of 14 spent using a preferred substance) are both bounded counts variables. We therefore will assume (a) whether an item is correct on the knowledge survey follows a Bernoulli distribution and the number of days out of 14 spent using a substance follows a binomial distribution, and (b) these distributions (both the binomial and Bernoulli) are governed by a latent probability parameter. This latent probability describes either the likelihood of getting an item correct on the knowledge survey or the average number of days spent using a preferred substance out of 14, and the log-odds for a student's latent probability at the three assessment time points is described following a trivariate normal distribution. This statistical model will allow us to examine changes in substance use and knowledge about substances while controlling for (1) measurement error, and (2) correlations between repeated measures collected over the three time points. The means for the log-odds of the latent probabilities can be further decomposed into a summation of population-level, school-level, and student-level effects. The specific decomposition of the means for the log-odds will depend on the outcome measure.

The complexity of the statistical models (e.g., a multivariate latent measure model with both fixed and random effects and with observed data distributed as counts) is most easily handled within a Bayesian framework. However, prior distributions will need to be defined for model parameters. A conservative approach will be taken using only weakly informative priors with a diffuse range (for example, standard deviations for log-odds will be set to 2.5, estimates for fixed effects will be centered at 0, and we will use empirical Bayes priors for intercepts).

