#### 2.10.6. Covariates

The covariates we will consider, at a minimum, are: (a) two terms implementing a quadratic trend for number of months since the start of the program, (b) a student's preferred substance (i.e., alcohol, cannabis, or nicotine), (c) a student's baseline level of dependence for his or her primary substance (based on appropriate self-report questionnaires), (d) number of repeat substance use infractions that a student has, (e) number of peers who use drugs, (f) a student's age at baseline, (g) a student's gender (or if cell counts are too low, biological sex), and (h) whether school is urban, rural, or suburban. These covariates will be used as part of missing data imputation, and if necessary, may be included in the primary analysis (to be determined during the analyst-blind period). If any additional covariates will be deemed necessary for inclusion, this will be done before the blind is broken for the analyst.

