#### 2.10.10. Sensitivity analyses

For all outcomes, we will conduct at least five sensitivity analyses. We will examine how robust our conclusions are to implementation of the intent-to-treat approach and also conduct an as-treated analysis, restricting comparisons for the key effect to students confirmed to have received standard disciplinary action pre-intervention vs. students confirmed to have attended iDECIDE sessions post-intervention. We will examine how robust our conclusions are to the assumption of additivity with the quadratic time trend and will fit an interaction model to examine (a) the statistical significance of the interaction terms between the key comparison and the quadratic time trend, and (b) the difference in performance on the leave-one-out cross-validation (LOO-CV) approximation between the additive and interaction models. We will examine how robust our conclusions are to the assumption of additivity with the three types of substances (alcohol, nicotine, and cannabis) and will again fit an interaction model and examine (a) the statistical significance of the interaction terms between the key comparison and the categorical predictors for substance type, and (b) the difference in performance on the LOO-CV approximation between the additive and interaction models. We will examine how robust our conclusions are to our missing data approach, rerunning the primary analysis using only observed data. Finally, we will examine how robust our conclusions are to implementation of the IPW approach, rerunning the primary analysis without inclusion of the stabilized weights.

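### The substance-use endpoint counts self-reported days on one preferred substance, so a move to another drug can score as improvement; urinalysis enters no stated analysis and the listed assays do not cover alcohol.

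*Protocol article*

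**What the plan says.** All references are to the protocol article.

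- **Endpoint.** Section 2.8.2: "Substance use behavior will be assessed by how many days of the past 14 days a student spent using their preferred substance". Section 2.10.1 names the two primary outcomes as "items correct on a knowledge survey and number of days out of 14 spent using a preferred substance", and section 2.10.9 refers to the same day count again.
- **Source.** Section 2.8.2: "Self-reported substance use will be assessed at all visits using the Timeline Followback". At follow-up, "a modified Timeline Followback will be administered at subsequent visits to ascertain substance use in the period between visits". The follow-up instrument is not worded as limited to the preferred drug.
- **Preferred substance.** Section 2.10.6 lists as a covariate the student's "preferred substance (i.e., alcohol, cannabis, or nicotine"). Section 2.10.7 places the same item among the baseline characteristics used for imputation.
- **Model.** Section 2.10.3 includes fixed effects for differences in days of use across alcohol, cannabis and nicotine. It does not say whether a student contributes one count or several.
- **Urine.** Section 2.8.2: "Urine samples will be collected at all three visits to biochemically verify self-reported use". Table 2 lists urinalysis under primary outcomes. The assays are a 10-panel dip test plus quantitative THCCOOH and cotinine.
- **Sensitivity analyses.** Section 2.10.10: "For all outcomes, we will conduct at least five sensitivity analyses". The five described are as-treated, time-trend interaction, substance-type interaction, observed data only, and no weights.
- **Claim.** The Introduction's hypothesis is about frequency of substance use, and Table 3 labels its rows by substance use. Section 2.7.2: "iDECIDE is drug agnostic, covering psychoeducational material relevant to alcohol, cannabis, nicotine, and other drugs".

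**The concern.** The endpoint is narrower than the conclusion drawn from it. If the preferred substance is set at baseline, use of any other drug at follow-up is invisible to the count. A student who replaces one drug with another then looks the same as a student who cuts down. That matters for a programme meant to act on all drugs, and more so because section 2.10.4 tests this endpoint for non-inferiority, where an error that lowers the count in the exposed phase favours the programme.

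Urine could be a check on the self-report, but the article does not carry it through. It stands under primary outcomes in Table 2, is absent from the two primary outcomes in section 2.10.1, and appears in neither the frequency model nor the five described sensitivity analyses. For students whose preferred substance is alcohol, the listed assays cannot verify the report at all.

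**Working it through.** **1. Is the endpoint one substance or several?** Sections 2.8.2, 2.10.1 and 2.10.9 all speak of one preferred substance, and section 2.10.7 treats it as a baseline characteristic with one of three values. Section 2.10.3 can be read in two ways: as an adjustment for which substance is the preferred one, or as a model with a separate count per substance. Section 2.10.6 lists preferred substance as a covariate in its own right, so the question stays open. The first reading agrees with the outcome definition; the second does not.

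**2. One student (invented figures).** Cannabis, the preferred substance, falls from 6 to 2 of 14 days, and nicotine starts on 10 days.
- Preferred-substance odds ratio: (2/12) / (6/8) = 0.22, an apparent benefit.
- Any-use days at follow-up lie between 10 (full overlap) and 12 (no overlap): (10/4) / (6/8) = 3.33 and (12/2) / (6/8) = 8, a worsening.

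**3. Group illustration (assumed inputs).** Let p be the share of days on the preferred substance and s the share of those days moved to another drug, with total days of use unchanged. The observed ratio is 1 − s and the observed odds ratio is odds(p(1 − s)) / odds(p).

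| p | s = 5% | s = 20% |
|---|---|---|
| 0.3 | 0.93 | 0.74 |
| 0.5 | 0.90 | 0.67 |
| 0.7 | 0.85 | 0.55 |

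At s = 20% the ratio is 0.80, the effect assumed in section 2.10.12 (1 versus 0.8). This shows how sensitive the endpoint is. It does not predict what will happen.

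**4. The margin, and what a small shift does to it.** Section 2.10.4 gives a pooled upper limit of 0.92: 1/0.92 = 1.087, stated as 1.09, and 1 + 0.09/2 = 1.045, as stated. Suppose true use worsens by exactly OR 1.045, and a share s of exposed students drops to 0 days by switching or denial. The share that returns the point estimate to OR 1.00 solves p1(1 − s) = p0, with odds(p1) = 1.045 × odds(p0):
- 3 of 14 days: p1 = 0.2218, s = 3.4%
- 5 of 14 days: p1 = 0.3673, s = 2.8%
- 8 of 14 days: p1 = 0.5822, s = 1.8%

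This moves only the point estimate. A rough standard error can be worked back from the stated power of 0.82 for a ratio of 0.8. I assume a two-sided 0.05 level for the power figure, which the article does not give, and convert the ratio to log-odds. SE = −ln(OR at ratio 0.8) / (1.96 + 0.915).
- 3 of 14 days: OR 0.759, SE 0.096. An estimate of 1.00 has upper limit exp(1.96 × 0.096) = 1.21.
- 8 of 14 days: OR 0.632, SE 0.160, upper limit 1.37.

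Both limits exceed 1.045, so non-inferiority would not be shown. The estimate would have to fall to 1.045/1.21 = 0.87 or 1.045/1.37 = 0.76. From a true OR of 1.045 that takes a differential of about 14% (3 of 14 days) or 13% (8 of 14 days).

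**5. Assay coverage.** The dip panel covers amphetamines, cocaine, barbiturates, methamphetamines, benzodiazepines, opiates, cannabinoids, phencyclidine, oxycodone and methadone. The quantitative assays add THCCOOH and cotinine. Cannabis and nicotine have a marker; alcohol has none.

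**The case against.** The strongest reply has four parts.

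*The article is a condensed source.* A reader might infer that a contradicting urine result is ignored. The text does not say so. It gives urine a verification role, the five sensitivity analyses are a stated minimum, and a rule for discordant results may stand in an analysis plan that is not shown. Only the narrower statement stands: urine enters no analysis the article describes, although Table 2 lists it under primary outcomes. Table 2 is a schedule of assessments and may simply group urinalysis with the outcome it supports, so the label is an ambiguity to clear up rather than a serious fault.

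*Preference might be updated at each visit.* The student in the illustration would then count as worse. Section 2.8.2 does not rule this out; section 2.10.7 points the other way. The text needs settling either way.

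*A tight margin does not mean that a tiny shift decides the trial.* A reader might infer that a 2% to 3% differential would produce a false non-inferiority finding. It would not: that shift only returns the point estimate to 1.00, and at the precision implied by the stated power roughly 13% to 14% would be needed.

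*Differential under-reporting is unproven.* Assessors are blinded to phase, data go to the hospital evaluation team rather than the school, confidentiality is protected, and dip results are shown to the assessor during the visit. These points stand. The documents contain no rate of denial or switching.

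Preferred-substance days is also a defensible choice of endpoint: an any-substance count may be dominated by frequent nicotine users. That is a reason to keep any-use supportive, not to leave it out.

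**Conclusion.** The point holds as a mismatch between endpoint and claim. On the plain reading, the analysed outcome is self-reported days on one preferred substance, apparently fixed at baseline, while the hypothesis and Table 3 refer to substance use as a whole. A move to another drug would count as improvement. The direction of this error is clear; its size cannot be estimated from the documents, and the figures above are illustrations under assumed values of p and s. The standard error behind the 13% to 14% figure is itself a rough back-calculation.

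Two further statements hold on the text. Section 2.10.3 does not fit cleanly with sections 2.8.2, 2.10.1 and 2.10.7 and must be reconciled with them. The verification statement is too broad, because alcohol is one of the three preferred substances and has no marker among the listed assays.

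The documents do not support requiring any-use days to pass the 1.045 test as well. That margin was derived from cannabis evidence, and a second required test would change the power. This is a worthwhile, inexpensive improvement, not a flaw that invalidates the primary analysis.

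**What to change.** - **(a) Define the count.** State that the preferred substance is fixed at baseline and whether the frequency model holds one count or several per student. Align section 2.10.3 with section 2.8.2.
- **(b) Add a supportive any-use analysis.** From the same Timeline Followback, derive days out of 14 with use of any substance. Analyse it with the same model and report the estimate and interval by phase, with no separate gate and no 1.045 test. Word the Table 3 conclusion as preferred-substance use unless the any-use result points the same way.
- **(c) Add a urine-discordance sensitivity analysis.** Where THCCOOH or cotinine contradicts a follow-up report of no cannabis or no nicotine use, set that report to missing and impute it rather than count it as 0 days. Report discordance by phase.
- **(d) Correct the wording.** Limit the verification statement to the substances assayed, which do not include alcohol, and label urinalysis in Table 2 as verification.

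**Cost.** Wording changes and two extra model runs on data already collected. They can be settled during the analyst-blind stage described in section 2.6. Any-use days may be dominated by frequent nicotine users, a positive THC result may reflect earlier use, and urine cannot be converted into a number of days. Both added analyses are therefore supportive only.
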